**3. GENERAL INFORMATION**

**3.1. CODE**

EL-DSG/07/2011

**3.2. TITLE**

Lymphocytic enteritis with negative coeliac serology and clinical response and histology with a gluten-free diet: double-blind randomized clinical trial with rechallenge of gluten vs. placebo.

**3.3. TYPE OF TRIAL**

Phase IV clinical trial.

**3.4. DESCRIPTION OF THE STUDY THERAPY**

Gluten is a protein found in cereals such as wheat, oats, rye, and barley, made up of gliadins and glutenins. It is therefore widely present in foods. The average daily intake of gluten is 20 grams.

Gluten will be administered in 10-gram sachets.

**3.8. EXPECTED DURATION OF TRIAL**

Maximum recruitment period: 30 months

Maximum treatment period: 6 months

Maximum total duration: 36 months

**4. JUSTIFICATION AND OBJECTIVES**

**4.1. JUSTIFICATION**

In recent years the concept of coeliac disease (CD) has undergone a profound re-examination. A wide range of clinical manifestations and histological presentations has been recognized, and significant progress has been made in learning about the genetic and immunological mechanisms that underlie the disease. The common denominator for all CD patients is the presence of a variable combination of clinical manifestations that are gluten-dependent and antibody-specific (tissue anti-transglutaminase 2, anti-endomysium), with the haplotypes HLA-DQ2 and/or DQ8 and various degrees of enteropathy ranging from epithelial lymphocyte infiltration (lymphocytic enteropathy, LE) to complete villous atrophy (1).

In addition, there is another condition known as non-coeliac gluten sensitivity (NCGS), the exact nature and limits of which, and the degree to which it may overlap with CD, are as yet poorly understood (2, 3). At present NCGS takes in a series of morphological, functional, and immunological alterations occurring in the absence of any of the key characteristics of CD (enteropathy, associate HLA haplotypes, and the presence of anti-tTG2 antibodies) but with a clinical response to the exclusion of dietary gluten (4). Along this line, patients have been described with NCGS without enteropathy (Marsh 0). Other patients have been described with only minimal changes in the mucus membrane—that is, with enteropathy (LE, Marsh 1). Unlike CD, NCGS is not associated with a genetic predisposition; it may be reversible, and the gluten-free diet for it needn’t be as strict as that for CD. In recent years, many patients have been diagnosed in our service with enteropathy that is sensitive to gluten, within the CD spectrum, on the basis of the presence of LE, positive coeliac genetic study, and clinical and histological response to a gluten-free diet, despite their having negative specific serology. On the basis of current understanding we wondered whether these patients presented CD, or whether some of them may in fact have an NCGS. Being able to assess the clinical and histological response to the reintroduction of gluten, as well as being afforded the chance to make specific immunological determinations in the intestinal mucosa, would allow us to make a definitive diagnosis of CD in these patients. Adhering to a gluten-free diet for life is no easy matter; for this reason alone a diagnosis of CD should be based on definitive evidence. Therefore, the results of the present study should go a long way toward broadening the spectrum of what today is called CD, and should also be of wide applicability in normal clinical practice.

**4.2. OBJECTIVES**

To demonstrate hypersensitivity to gluten in patients with lymphocytic enteropathy and a clinical and histological response to a gluten-free diet in spite of presenting IgA negative tissue anti-transglutaminase antibodies.

**5. TYPE AND DESIGN OF CLINICAL TRIAL**

This is a phase IV double-blind clinical trial, controlled with placebo in parallel and with random assignment of treatment type.

**5.1. RANDOMIZATION**

A 1:1 proportion will be followed in making random assignment of participants to treatment groups. Assignment will be made using a computer, and medication coded consecutively with numbers for dispensation, following a double-blind schema, in the hospital pharmacy at the admission of each subject to the study.

On day 1 of the study each randomized patient will receive a participant number which will also be used for his or her medication. This randomized number will be associated with a specific treatment.

**5.2. MASKING METHODS**

In order to mask the gluten and placebo supplements they will be given the same organoleptic characteristics. They will be administered in non-transparent sachets filled with dry powder, with no difference in appearance between the consecutively numbered product packaging for the two treatment groups.

**6. SUBJECT SELECTION**

**6.1. INCLUSION CRITERIA**

1. Signed informed consent

2. Age 18 or older

3. Confirmed histological diagnosis of lymphocytic enteropathy (LE)*

5. Coeliac-positive genetic study (HLA-DQ2 and/or HLA-DQ8)

6. Negative coeliac serology

7. Complete clinical and histological response to gluten-free diet

8. Initial clinical signs with or without extra-intestinal manifestations

*Lymphocytic enteropathy is defined as an intraepithelial lymphocyte count greater than 25 per 100 epithelial cells, using histochemical techniques with anti-CD3 monoclonal antibodies for the count.

**6.2. EXCLUSION CRITERIA**

1. Inability to adhere to the scheduled visits or other protocol requirements, in the judgement of the investigator

2. Participation in a clinical trial in the previous 30 days, simultaneous participation in a trial, or prior participation in the present study

3. History of gluten-sensitive enteropathy with villous atrophy or positive serology

4. Lymphocytic enteropathy or initial response to gluten-free diet but following a normal diet at the time of selection

**6.3. EXPECTED NUMBER OF SUBJECTS**

The estimated sample size is 20 patients (10 for each treatment group) who will be evaluated on the basis of intention to treat.

**7. DESCRIPTION OF TREATMENT**

The subjects included in the study will be randomly distributed to two therapeutic groups. The randomly assigned code of each will determine which of the two treatment options is followed:

**Group 1 (Group without gluten)**: Will follow a gluten-free diet and will receive placebo as supplement (10 grams of powdered maltodextrin; Appendix 2), 1 sachet every 12 hours, mixed with food (puree, soup).

**Group 2 (Group with gluten)**: Will follow a gluten-free diet and will receive gluten as supplement (10 grams of powdered gluten; Appendix 1), 1 sachet every 12 hours, mixed with food (puree, soup).

**7.1. CONCOMITANT TREATMENT**

Any medication that needs to be taken will be noted on the page for this purpose in the data collection documentation.

**7.2. MEANS TO ASSESS COMPLIANCE**

Assessment of compliance will be made by counting the number of sachets returned at each visit and by reviewing what is recorded in the patient diary.

A standard gluten-free diet will be prescribed in writing. A dietician or expert nutritionist will see each patient each month to evaluate how closely the diet is being followed (Appendices 4 and 5).

**7.3. GUIDELINES FOR MANAGEMENT OF STUDY MEDICATION**

The distribution of the medication samples for the clinical trial will be made through the pharmacy service. The pharmacist/investigator will complete, and return to the sponsor, the sheets confirming receipt of the sachets of therapeutic material; they will be responsible for the proper handling and storage of the medication, and for that which is left over at the conclusion of the study. All medication used in the study must be stored in a secure location throughout the trial.

All of the medication will be carefully accounted for. At the conclusion of the study a copy of the inventory will be filed by the investigator. Leftover medication will be returned to the sponsor’s pharmacy service for destruction.

**7.4. PACKAGING AND LABELING**

The medication for the trial will be distributed to subjects in the form of sachets, either of gluten or maltodextrin according to the randomization status of the participant. The sachets will be numbered in correlated order and will be assigned in rigorous order in accordance with the inclusion of subjects in the study. The evaluator will at all times be blind to the randomization key.

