# 1. SUMMARY OF THE STUDY

| **Title** | Lymphocytic enteritis with negative coeliac serology and clinical and histological response to a gluten-free diet: double-blind randomized clinical trial with rechallenge of gluten vs. placebo. | |
| --- | --- | --- |
| **Study code** | EL-DSG/07/2011 | |
| **Objectives** | To demonstrate hypersensitivity to gluten in patients with lymphocytic enteritis, and clinical response and histology of a gluten-free diet despite the presence of IgA negative tissue anti-transglutaminase antibodies. | |
| **Treatment** | Sachets with gluten (10 g) or placebo (maltodextrin: 10 g): 1 sachet every 12 hours. | |
| **Study design** | Prospective, randomized, double-blind, placebo-controlled, with parallel groups of gluten rechallenge vs. placebo, for 24 weeks, in patients following a gluten-free diet.   - Group A: Powdered gluten (10 g every 12 hours) - Group B: Placebo (10 g every 12 hours)   Determination of digestive clinical state, adherence to diet, coeliac serology, histology, flow cytometry, and tissue anti-transglutaminase antibodies in intestinal mucus membrane, at baseline and after gluten rechallenge or placebo (whether clinical digestive symptoms reappear at 4 or 12 weeks, or at the conclusion of the study at 24 weeks). | |
| **Study population** | Inclusion criteria:  1. Signed informed consent  2. Age 18 or older  3. Confirmed histological diagnosis of lymphocytic enteropathy (LE)  5. Coeliac-positive genetic study (HLA-DQ2 and/or HLA-DQ8)  6. Negative coeliac serology  7. Complete clinical and histological response to gluten-free diet  8. Initial clinical signs with or without extra-intestinal manifestations | |
|  | Exclusion criteria:  1. Inability to adhere to the scheduled visits or other protocol requirements, in the judgement of the investigator  2. Participation in a clinical trial in the previous 30 days, simultaneous participation in a trial, or prior participation in the present study  3. History of gluten-sensitive enteropathy with villous atrophy or positive serology  4. Lymphocytic enteropathy or initial response to gluten-free diet but following a normal diet at the time of selection | |
| **Sample size** | 20 patients | |
| **Length of treatment** | 24 weeks | |
| **Primary efficacy variables** | Reappearance of clinical digestive signs and histological recurrence | |

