**8.3. DESCRIPTION OF METHODS USED TO ASSESS RESPONSE**

Clinical response will be measured with analogue visual scales ranging from 0 to 100, administered at baseline and at each visit up to 6 months, for symptoms of abdominal pain, abdominal swelling, diarrhea, and flatulence (total score 0 to 400 points) (Appendix 6).

Patient quality of life will be evaluated in the first visit and the last (at 6 months, or at early withdrawal) using the GIQLI questionnaire (Gastrointestinal Quality of Life Index), which has been shown to yield valid, reliable scores for the detection of significant clinical changes in the lives of patients regarding their health (Eypasch E et al. Gastrointestinal Quality of Life Index: development, validation and application of a new instrument. Br J Surg 1995; 82:216-22; Quintana JM et al. Translation and validation of the Gastrointestinal Quality of Life Index (GIQLI). Rev Esp Enferm Dig 2001; 93:693-706) (See Appendix 3).

At the first visit and the last (or at early withdrawal from the study) a distal duodenal biopsy will be drawn for histological study, and evaluation of tTG deposits and lymphocytic sub-populations (using flow cytometry) will be made.

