**8.4. WITHDRAWAL CRITERIA**

Any patient may withdraw from the study at any time without incurring any personal penalty and without the need for explanation. Withdrawal must be noted in the CRF when it occurs, along with the results to date and the reason(s) for withdrawal, if given.

The investigator may also withdraw a patient from the study upon consideration of the risks and benefits thereof, and determination that the former outweigh the latter with continued participation. The CRF must reflect the date and main cause for the withdrawal, as well as any further observations that may be made at the time of withdrawal. Among the reasons for withdrawing a patient early from the study are the following (the main reason should be indicated):

• Lack of efficacy of treatment, e.g.:

– Progression of the illness under study in comparison to baseline.

(in the six weeks following).

– The need to administer a concomitant medication that is prohibited in the treatment of the illness under study.

• Intolerable adverse events.

• Lack of patient cooperation, e.g.:

– Patient request.

– Lack of therapeutic compliance or failure to carry out visits according to the agreed calendar.

– Technical or logistical reasons (e.g., change of patient residence).

– Pregnancy or breast-feeding, either existing or planned.

• Others (must be noted), e.g.:

– Diagnosis different from that of the study.

All patients withdrawing early from the study must be seen within 7 days of the last administration of the medicine used in the study. This final visit is to be duly recorded in the CRF.

The investigator will continue to observe all patients withdrawing early from the study as a result of intolerable adverse events until the findings have been resolved.

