**13. STATISTICAL ANALYSIS**

The calculation for the sample size is based on the main variable of efficacy—that is, the rate of recidivism at 6 months. On the basis of results of previous studies it was determined that the rate of recidivism with the reintroduction of gluten would be 80%, and with placebo 20%. Assuming a 10% patient drop-out rate, an alpha value of 5%, and statistical power (beta) of 80%, for a bilateral test it was calculated that 10 patients would be needed for each patient group (bearing in mind that analyzing the results would require a Chi-square test with Yates correction). The total number, then, is 20 patients.

Excluded from this analysis are those subjects presenting significant departures from the protocol.

All of the evaluations of the primary and secondary variables, both of efficacy and of safety, are understood in the exploratory sense (alpha=0.05, bilateral).

The Chi-square test with Yates correction will be used for independent groups and the Fisher exact test for qualitative variables. For intergroup comparison of the quantitative variables, the Student-t test will be used for parametric variables, and the Mann-Whitney U-test for non-parametric variables.

The finding of values for differences of p less than 0.05 will be considered significant. The rates for clinical remission between treatment groups will be expressed proportionally with the corresponding bilateral interval of confidence of 95%, as an estimation of therapeutic effect.

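### Evaluator masking covers only the randomisation key, while the timing of the final biopsy carries information on relapse and, in part, on arm, so the protocol does not ensure that histology is read blind to clinical course

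*Protocol*

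**What the plan says.** On masking, section 5.2 provides opaque sachets with "no difference in appearance between the consecutively numbered product packaging for the two treatment groups", and section 7.4 adds that "The evaluator will at all times be blind to the randomization key". Neither goes further. The protocol does not say who the evaluator or the biopsy reader is, or what clinical information that reader receives.

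On timing, the Summary places the post-challenge assessments, histology and mucosal tTG antibodies included, at a point that turns on "whether clinical digestive symptoms reappear at 4 or 12 weeks, or at the conclusion of the study at 24 weeks". Section 8.3 says: "At the first visit and the last (or at early withdrawal from the study) a distal duodenal biopsy will be drawn for histological study". Section 8.4 lists progression of the illness among the reasons for early withdrawal, but also reasons unrelated to relapse, for example "Lack of therapeutic compliance or failure to carry out visits according to the agreed calendar".

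On the role of histology, the Summary names histological recurrence within the primary variables, whereas section 8.1 lists histological change as secondary. Section 6.1 defines lymphocytic enteropathy, for entry, as more than 25 intraepithelial lymphocytes (IEL) per 100 epithelial cells on anti-CD3 staining.

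**The concern.** In this design the date of the final biopsy is partly an outcome. Concealing the key does not conceal that date. A pathologist who sees a week-4 or week-12 request, or the reason for it, learns that the patient probably relapsed and can guess the arm better than chance in most settings. The guess is not even needed: knowing of the relapse is enough to colour a borderline count.

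An IEL count against a cut-off and the assessment of tTG deposits are human readings. Section 4.1 treats the histological response to reintroduced gluten, together with the clinical response and mucosal immunology, as the basis for a definitive diagnosis of coeliac disease. Histology serves that purpose only if it is evidence separate from symptoms. If knowledge of relapse enters the reading, the two results agree partly by construction, and the error favours the trial's hypothesis.

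**Working it through.** The plan gives no figure on this point, so there is none to reproduce.

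**Inputs from the protocol.** Allocation: "A 1:1 proportion will be followed" (5.1). Relapse at 6 months: 80% on gluten, 20% on placebo (13). Drop-out: 10% (13). Size: 10 per group (6.3).

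**Step 1, arm given relapse.** With equal allocation:

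- P(gluten given relapse) = 0.8 / (0.8 + 0.2) = 80%.
- P(placebo given no relapse) = 0.8 / (0.8 + 0.2) = 80%.

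**Step 2, arm given an early biopsy.** Let d be the share of each arm that leaves early for reasons other than relapse and is biopsied then. Let f be the share of relapses seen before week 24. The protocol does not give f. The early-biopsy rates are

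- gluten: E_g = d + (1 − d) × 0.8 × f
- placebo: E_p = d + (1 − d) × 0.2 × f

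and P(gluten given early) = E_g / (E_g + E_p). If d = 0 and f is equal in both arms, f cancels and the result is 80%. With d = 10%, assumed equal by arm and all biopsied early:

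| f (both arms) | E_g | E_p | Gluten, given early biopsy | Early biopsies not due to relapse: 2d / (E_g + E_p) | Gluten, given week-24 biopsy |
|---|---|---|---|---|---|
| 25% | 0.280 | 0.145 | 66% | 47% | 46% |
| 50% | 0.460 | 0.190 | 71% | 31% | 40% |
| 75% | 0.640 | 0.235 | 73% | 23% | 32% |
| 100% | 0.820 | 0.280 | 75% | 18% | 20% |

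**Step 3, unequal early shares** (gluten, placebo; d = 10%; shares assumed):

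- 100%, 50%: 0.82 / (0.82 + 0.19) = 81%
- 50%, 100%: 0.46 / (0.46 + 0.28) = 62%
- 75%, 25%: 0.64 / (0.64 + 0.145) = 82%

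The corners of a 25% to 100% range are wider. Shares of 25%, 100% give 0.28 / (0.28 + 0.28) = 50%, and 100%, 25% give 0.82 / (0.82 + 0.145) = 85%. Timing alone tells nothing about the arm only if gluten relapses come much later than placebo relapses.

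**Step 4, what a reading shift could do (illustration only).** Assume that gluten affects symptoms but not histology, that final IEL counts are normal with mean 20 and SD 6 in both arms, and that recurrence means a count above 25. None of the distribution figures comes from the protocol, and the cut-off is borrowed from the entry criterion. Then P(count > 25) is 20.2% unshifted, 36.9% at +3 cells, 9.1% at −3, 50.0% at +5 and 4.8% at −5.

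- Early slides read 3 cells higher, f = 75%, d = 0: gluten 0.60 × 36.9% + 0.40 × 20.2% = 30%; placebo 0.15 × 36.9% + 0.85 × 20.2% = 23%.
- Early slides +3 and week-24 slides −3, f = 100%, d = 0: gluten 0.80 × 36.9% + 0.20 × 9.1% = 31%; placebo 0.20 × 36.9% + 0.80 × 9.1% = 15%.
- The same with 5 cells: 0.80 × 50.0% + 0.20 × 4.8% = 41%; 0.20 × 50.0% + 0.80 × 4.8% = 14%.

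With d = 10% and every early slide read alike, using E_g and E_p from the table, the three become 31% v 24%, 32% v 17% and 42% v 17%.

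**The case against.** A reader might infer that histology is not read blind. The documents do not support that: no section says that the pathologist receives the date, the visit or the symptoms, and a guess about the arm is not knowledge of it. The sentence in 7.4 is not false either, since someone who knows of a relapse is still blind to the key. This stands. What can be said is that the protocol fixes masking too narrowly for its own biopsy schedule, not that masking fails.

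A reader might also infer that an early biopsy means a relapse and hence an 80% chance of gluten. Sections 8.3 and 8.4 also produce early biopsies after other withdrawals, and relapses first seen at week 24 share their date with symptom-free completers. The 80% is exact only for a relapse. This stands too.

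The illustrations rest on assumed counts and shifts. Two of the three need every relapse to be early and readings to move in both directions, which is extreme. The mildest, 30% v 23%, is 0.07 × 10 = 0.7 of a patient per group. If gluten had no effect on symptoms, relapse and its timing should be alike in the arms, and this mechanism would create no difference. All of this stands.

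Finally, 8.1 makes histology secondary, section 13 calls all evaluations exploratory, and the symptom scales are completed by patients, so slide reading cannot touch them. That limits the consequence but does not remove it, because the Summary places histological recurrence among the primary variables and 4.1 rests the diagnosis partly on it.

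**Conclusion.** The point holds in limited form. Section 7.4 masks the evaluator to the key only, the biopsy time point depends on clinical course, and no other section keeps time point or symptoms from the reader. The chance of gluten is 80% given a relapse. Given an early biopsy it is about 66% to 75% under 10% drop-out, equal by arm and biopsied early, with equal early shares of relapse. It is about 62% to 82% in the unequal cases tried, and 50% to 85% at the assumed extremes. Any effect on the histological comparison would run towards the hypothesis, but its size is unknown, and the recurrence rates above only show what assumed reading shifts would do. This is a cheap improvement, not a demonstrated loss of blinding. It is separate from the matter of unequal exposure at the time of biopsy.

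**What to change.** Add to section 8.3 that, for the trial endpoint:

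- baseline and final CD3-stained slides, and tTG-deposit preparations or images where these are kept, are recoded with random numbers, with date, visit, symptoms and reason for sampling removed;
- the existing pathologist reads them in random order after the last biopsy has been taken;
- only these readings enter the analysis.

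Routine reports for eligibility and care are issued as usual, so patient management does not change.

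The cost is recoding plus one re-read of about 20 × 2 = 40 existing slides, with no new biopsy and no extra reader. Trial histology becomes final only after the last patient. Some recall by a pathologist who also wrote the routine reports remains possible; recoding, random order and the delay reduce it but do not abolish it. The protocol does not say whether tTG images are stored, hence the qualification.
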